**B**. **Randomization**

Randomization will occur immediately after consent for study participation has been obtained from a parent/guardian and study eligibility confirmed. Subjects will be randomized in equal numbers to receive either the pneumococcal conjugate vaccine or placebo; the unique subject identification numbers will be assigned in sequence. Due to some mobility within Soweto, children may not always receive their routine immunizations at the same clinic. To facilitate this movement, children will be randomized at the time of their first immunization to one of 10 vaccination codes, designated 0-9. The vaccination code and subject ID number will be recorded on the child’s Road to Health card, on the clinic medical records, and on the clinic immunization register. Immunization sites will be provided with vials for each of the 10 vaccination codes, thereby allowing children to receive their study immunizations at any of the study sites. Randomization schemes for each recruitment site will be generated prior to the start of the study by a statistician from WLVP who is otherwise uninvolved with the study.

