**A. Primary outcome variables**

1. Cases (see Section VIII for case definition) of vaccine-serotype pneumococcal invasive disease in children who have completed the three-dose series per protocol.

2. Cases (see Section VIII for case definition) of radiologically-confirmed hospitalized pneumonia in children who have completed the three-dose series per protocol.

Outcomes will qualify for the primary analysis of they occur at least 14 days after the third dose of vaccine/placebo. Outcome ‘1' will be the basis for the vaccine efficacy estimate. Since the prevalence of radiographically-confirmed severe pneumonia may be several-fold higher than that of culture-confirmed pneumococcal invasive disease (to be estimated from the ongoing pneumonia surveillance study) and the mortality rate from severe pneumonia is probably high (to be estimated from the ongoing pneumonia surveillance study), outcome ‘2' will be used to assess the effectiveness of the vaccine in reducing the overall pneumonia disease burden and its impact on public health as well as to estimate the proportion of severe pneumonia caused by pneumococci of vaccine serotypes.

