The current estimate of the incidence of invasive pneumococcal disease in children under the age of 2 years in Soweto is 160/100,000 child years [12]. Assuming that 70% of the disease cases are due to the vaccine serotypes, the vaccine-serotype disease rate is 112 cases per 100,000 child years. Based on this estimate of disease rate and the assumption that the true vaccine efficacy is 70%, approximately 19,231 child years follow-up per treatment group will be needed to accrue 28 cases of vaccine-serotype disease in HIV-uninfected children. The annual birth cohort in Soweto is approximately 24,000 infants, 4% (960) of whom would be expected to be HIV-infected. Allowing for loss to follow-up, the entire birth cohort over a two year period will be recruited to reach the targeted enrolment goal. The study is expected to accrue 28 cases of vaccine-serotype disease in HIV-uninfected children in approximately 32 months. Approximately 29,533 child years of follow-up per treatment group, expected in approximately 39 months, will be needed to accrue 43 cases. A more accurate estimate of the disease rate is expected to be obtained prior to the start of the study from the prospective cohort study currently underway in Soweto.

The rate of hospitalized pneumonia (Primary Outcome ‘2') will be compared between the treated and the control group using a Poisson regression, with age category and calendar month of the third dose (season category) as possible stratification variables. An estimate of the rate reduction and its confidence interval will be obtained from the Poisson regression. Multiple events of an individual will be included in the rate estimates. The null hypothesis is that there is no rate reduction and will be tested based on the Poisson regression with a two-tailed  = 0.05. An analysis to compare the number of children with at least one event between the two groups will also be performed.

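### The primary test and interval for hospitalized pneumonia come from a Poisson regression that counts a child's repeat admissions, with no stated allowance for within-child correlation, so the 5% level is not assured.

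*Protocol*

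**What the plan says.** Section IX.A lists two primary outcome variables. The second is "Cases (see Section VIII for case definition) of radiologically-confirmed hospitalized pneumonia in children who have completed the three-dose series per protocol".

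Section IX.B then sets its analysis:

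- Model: the rate "will be compared between the treated and the control group using a Poisson regression, with age category and calendar month of the third dose" as possible stratification variables.
- Estimate and interval: "An estimate of the rate reduction and its confidence interval will be obtained from the Poisson regression".
- Repeat episodes: "Multiple events of an individual will be included in the rate estimates".
- Test: "The null hypothesis is that there is no rate reduction and will be tested based on the Poisson regression with a two-tailed" significance level of 0.05.
- Further analysis: "An analysis to compare the number of children with at least one event between the two groups will also be performed".

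The case criteria for this outcome in Section VIII.B contain no first-episode limit and no minimum gap between admissions. Section VIII.A, by contrast, limits invasive disease (Primary Outcome 1) to the first episode. No robust, clustered or scaled variance, negative binomial model or frailty term is named for the pneumonia analysis.

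**The concern.** The Poisson model sets the variance of the event total equal to its mean. That is right if every child has the same underlying rate and episodes in one child occur independently. It fails if some children are more prone to pneumonia than others, or if one admission makes another more likely. The variance of the total then exceeds its mean, and a model-based standard error is too small.

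The protocol itself gives reasons to expect this. Section III lists overcrowding, pollution, passive smoking and crèche exposure as risk factors, and these differ between households. Section VIII.C.1 has radiographs read admission by admission, so a readmission with unresolved consolidation could count as a second event.

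At stake is one of the two primary hypotheses. The error runs one way: the interval is too short, and a chance difference is declared significant more often than the stated 5%. Primary Outcome 1 is not affected, because it counts first episodes only.

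**Working it through.** **Inputs from the protocol.** Poisson regression, all episodes counted, two-tailed 0.05 (Section IX.B). Primary status (Section IX.A). No recurrence rate is given, and the power calculation for this outcome is deferred until the surveillance study provides a rate (Section IX.B).

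**Assumption.** The share q of affected children who have another episode is not in the document. A range of 0% to 20% is used.

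**Step 1. The plan's own figure.** Let φ be the ratio of the true variance of the event count to its Poisson variance. The type I error of a nominal two-sided 5% Wald test with model-based variance is

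α = 2 × [1 − Φ(1.96 / √φ)].

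With φ = 1 this gives 0.050, the stated level. Counting repeats does no harm by itself; the level fails only when φ exceeds 1.

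**Step 2. Variance ratio when some children recur.** For rare events, φ is approximately E[N²] / E[N] among children with N ≥ 1 episodes.

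- At most two episodes: φ = [(1 − q) + 4q] / [(1 − q) + 2q] = (1 + 3q) / (1 + q).
- Geometric recurrence: φ = (1 + q) / (1 − q).

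The correct interval is wider than the model-based one on the log scale by √φ.

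| q (assumed) | φ, at most two | √φ | α | φ, geometric | α |
|---|---|---|---|---|---|
| 0% | 1.000 | 1.00 | 5.0% | 1.000 | 5.0% |
| 2% | 1.039 | 1.02 | 5.5% | 1.041 | 5.5% |
| 5% | 1.095 | 1.05 | 6.1% | 1.105 | 6.2% |
| 10% | 1.182 | 1.09 | 7.1% | 1.222 | 7.6% |
| 20% | 1.333 | 1.15 | 9.0% | 1.500 | 11.0% |

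**Step 3. Refinement.** The exact ratio is E[N²] / E[N] minus the mean number of episodes per child, since a few repeats occur even under equal risk. At an assumed mean of 0.03, the at-most-two values of φ for q = 2%, 5%, 10% and 20% become 1.009, 1.065, 1.152 and 1.303, and α becomes 5.1%, 5.8%, 6.8% and 8.6%. The direction is unchanged. At 2% recurrence the effect nearly disappears.

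**Step 4. Simulation with no vaccine effect.** There were 20,000 children per arm and 4,000 trials per scenario. Risk varied between children by a gamma frailty with variance k, and m is the mean number of episodes per child (both assumed). Under this model φ = 1 + km.

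| m | k | Poisson, model-based | Poisson, child-clustered variance | At least one event |
|---|---|---|---|---|
| 0.02 | 0 | 4.6% | 4.6% | 4.8% |
| 0.02 | 5 | 6.5% | 5.1% | 5.1% |
| 0.04 | 5 | 7.2% | 5.0% | 5.1% |
| 0.04 | 10 | 10.1% | 5.2% | 5.4% |

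The formula gives 5.0%, 6.2%, 7.4% and 9.8% for the model-based column, in line with the simulation. The clustered variance restores the level in every scenario.

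**The case against.** **The variance estimator is not stated.** A reader might infer that the protocol prescribes an ordinary Poisson analysis treating repeat admissions as independent. It does not say so. A robust or scaled variance fits inside a Poisson regression, and an analysis plan that is not shown could specify one. This stands as a limit on the wording. It does not remove the point: the protocol fixes the model, the source of the interval and the test, includes repeats, and requires no correction.

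**The inflation is conditional.** A reader might also infer that the type I error definitely exceeds 5%. The document does not support that either. With equal risk and separate episodes the level holds, and no recurrence figure is given.

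**The protocol's own figures suggest the lower end.** Appendix 1 gives 1,478 bronchopneumonia admissions in 1995, and Section I.D puts 69.2% of pediatric admissions under 2 years. Over two birth cohorts (48,000 children), 1,478 × 0.692 / 48,000 is about 2.1% per year. Removing the 30% of admitted children who were HIV-infected (Section I.E) leaves about 1.5%. With 19,231 to 29,533 child years per group (Section IX.B) over about 24,000 children, the mean is about 0.012 to 0.018 episodes per child. With frailty variance 1, 5 or 10 (assumed), φ = 1 + km gives α of about 5.1% to 5.2%, 5.7% to 6.0%, or 6.4% to 7.1%. This is rough: admissions were rising, Orange Farm adds children, and radiological confirmation removes cases. It does make the 20% row look extreme for HIV-uninfected children.

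**A comparison free of the problem is already planned.** The analysis of children with at least one event holds its level in the simulation. However, Section IX.B describes it as an additional analysis and ties the null hypothesis and the 0.05 level to the Poisson regression. If the two disagree, the exposed test is the one the protocol names.

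**Strata and site.** A reader might infer that leaving recruitment site out of the model, although "Randomization schemes for each recruitment site will be generated prior to the start of the study by a statistician", adds to the inflation. It does not: omitting a stratification factor tends to be neutral or conservative for type I error. The optional strata are not part of this point.

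**Conclusion.** The point holds in conditional form. The protocol ties the primary test and interval for hospitalized pneumonia to a Poisson regression that counts repeat admissions, without any stated allowance for within-child correlation. If model-based variance is used and children differ in risk, the interval is too narrow and the 5% level is not assured.

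The size rests on an assumed recurrence rate. The inflation is small to moderate, about 5.5% to 7%, if 2% to 10% of affected children have a second episode. It reaches about 9% to 11% only if 20% do. The direction of the error is firm; its size is not. The efficacy estimate for invasive disease, which Section IX.A bases on Primary Outcome 1, is untouched.

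**What to change.** Add one sentence to Section IX.B. The rate ratio for Primary Outcome 2 is estimated by Poisson regression on all qualifying episodes, and its confidence interval and two-tailed 0.05 test use a robust (sandwich) variance clustered on the child. A negative binomial model is an acceptable alternative, provided one of the two is named as primary in advance. Keep the comparison of children with at least one event and label it supportive.

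The change needs no further data or participants. Its cost is an interval wider on the log scale by about 2% to 9% if 2% to 10% of affected children recur, about 15% at 20% recurrence with at most two episodes, and essentially unchanged if there is no excess variation.

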Subjects will be randomized at each recruitment site in equal numbers to receive either the pneumococcal conjugate vaccine or placebo; there will be ten vaccine groups, designated 0-9. Randomization schemes for each recruitment site will be provided prior to the start of the study by WLVP. Each study subject will receive three injections of either pneumococcal conjugate vaccine or placebo, administered concurrently with TETRAMUNE® (DTPHib), OPV, and Hep B. The injections will be administered at approximately 6, 10, and 14 weeks of age, with a minimum interval of 3 weeks between each dose and all three doses being completed by 9 months of age, as per protocol. Vaccine safety will be evaluated by monitoring each child for approximately 15 minutes after vaccination; the parent/guardian will also be asked to observe for untoward effects which might occur within one week of vaccination. Study pediatricians will conduct daily surveillance for hospitalization of study participants. The frequency of adverse events following vaccination will be assessed for both the placebo and treatment groups.

Vaccine efficacy will bedefined as the number of cases of culture-confirmed invasive pneumococcal disease or pneumonia requiring hospitalization, in the HIV-negative group receiving the pneumococcal conjugate vaccine compared to the number of cases occurring in the placebo group. The study pediatricians will conduct daily surveillance, including ward visits, at Chris Hani Baragwanath Hospital, the referral hospital for Soweto and surrounding area. They will also obtain daily lists from the hospital microbiology laboratories of patients with specimens positive for *S. pneumoniae* confirmed pneumococcal disease. HIV testing will be performed in an anonymous manner for all children with study outcomes who are not tested for HIV during hospitalization. Those outcome cases with no HIV test results will be excluded from the efficacy analyses but will be included in the “intent to treat” analysis.

No formal interim analysis of the efficacy data is planned and no early termination of the study due to early evidence of efficacy is planned. Once 28 HIV-negative “primary objective 1" outcome cases have been accrued, enrolment into the study will stop. The International Advisory Committee for the study will then meet to discuss whether/how long surveillance for outcome cases should continue. Surveillance will likely continue until 43 total cases have been accrued.

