**B. Statistical analyses for the primary outcome variables**

Efficacy of the vaccine will be estimated by comparing the incidence rates of vaccine-serotype invasive pneumococcal disease (Primary Outcome ‘1') between the recipients of three doses of the vaccine and placebo. Efficacy will be estimated as (1-RR) x 100%, where RR is the ratio of the incidence rate of the treated group versus that in the control group. With individualized randomization of a large cohort at a 1:1 allocation ratio, the follow-up time in the treated and control groups should be equal. The rate ratio can, therefore, be estimated as the ratio of the number of cases in the treated group versus that in the control group.

An exact two-sided 95% confidence interval for vaccine efficacy will be estimated, based on the binomial distribution for the number of cases among vaccinees, given the total number of cases and the ratio of follow-up time in placebo recipients to follow-up time in vaccine recipients. The statistical power for this analysis depends on the true efficacy and the number of accrued cases. For power calculations, we assume the true efficacy against vaccine-serotype invasive disease is 70% and that the ratio of follow-up times is 1. Then 28 cases are required for an 80% probability that the lower limit of the 95% confidence interval for efficacy will be greater than 0 (i.e., to reject the hypothesis of no efficacy); for an 80% probability that the lower limit will be greater than 20% 43 cases are required. We plan to enrol study infants until 28 HIV-uninfected vaccine-serotype cases have been accrued for the primary analysis and then continue surveillance until a total of at least 43 cases have been accrued. The following cases splits, out of the 28 cases, can lead to rejection of the null hypothesis.

| Control Cases | Treated  Cases | Estimate of vaccine  efficacy (%) | Lower 95% Confidence  Limit of VE (%) |
| --- | --- | --- | --- |
| 28 | 0 | 100 | 85.9 |
| 27 | 1 | 96.3 | 77.5 |
| 26 | 2 | 92.3 | 69.2 |
| 25 | 3 | 88.0 | 60.6 |
| 24 | 4 | 83.3 | 51.4 |
| 23 | 5 | 78.3 | 41.5 |
| 22 | 6 | 72.7 | 30.6 |
| 21 | 7 | 66.7 | 18.6 |
| 20 | 8 | 60.0 | 5.1 |

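### Both primary outcomes are tested at the full two-sided 0.05, and the protocol's emphasis on invasive disease is not written as a testing rule

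*Protocol*

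**What the plan says.** Section IX.A lists two primary outcome variables: "Cases (see Section VIII for case definition) of vaccine-serotype pneumococcal invasive disease in children who have completed the three-dose series per protocol", and "Cases (see Section VIII for case definition) of radiologically-confirmed hospitalized pneumonia in children who have completed the three-dose series per protocol". Each has its own test in section IX.B.

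- **Outcome 1 (invasive disease).** "An exact two-sided 95% confidence interval for vaccine efficacy will be estimated, based on the binomial distribution for the number of cases among vaccinees". A lower limit above 0 is the criterion ("i.e., to reject the hypothesis of no efficacy").
- **Outcome 2 (pneumonia).** "The null hypothesis is that there is no rate reduction and will be tested based on the Poisson regression with a two-tailed" level of 0.05.

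The protocol gives the two outcomes different weight. Section IX.A makes Outcome 1 the basis of the efficacy estimate, whereas Outcome 2 "will be used to assess the effectiveness of the vaccine in reducing the overall pneumonia disease burden and its impact on public health". Section IX.B derives the 28- and 43-case targets from Outcome 1 alone, and enrolment stops on Outcome 1 cases.

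Other places put pneumonia on the same footing. The Protocol Summary counts both case types when it defines vaccine efficacy ("culture-confirmed invasive pneumococcal disease or pneumonia requiring hospitalization, in the HIV-negative group receiving the pneumococcal conjugate vaccine compared to the number of cases" on placebo), and section V.F.3 is similar. Section VIII.B sets entry criteria for a second primary efficacy calculation. Section VIII.C.1 says that its radiological definition serves the primary analysis of efficacy against pneumonia.

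The protocol gives no testing order, no division of alpha, and no statement whether success needs one outcome or both.

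**The concern.** With two primary tests, each at the full level, the chance that at least one is falsely significant exceeds the level of either, unless a rule links them. The emphasis in section IX could serve as that rule but is not written as one, and the Summary and sections V.F.3 and VIII pull the other way.

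The gap matters most if the outcomes disagree. Suppose invasive disease splits 19 control to 9 vaccine cases, which lies just outside the rejection table in section IX.B, and pneumonia gives p = 0.04. The protocol does not say whether that is a positive trial, a supportive finding, or one success and one failure. The question would then be settled after unblinding, when any answer is open to dispute.

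**Working it through.** **Inputs from the protocol (section IX.B).** 1:1 follow-up; assumed true efficacy 70%; targets of 28 and 43 cases; Outcome 1 rejected when the exact two-sided 95% lower limit is above 0; Outcome 2 tested at two-tailed 0.05.

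**Inputs assumed.** Both nulls are true; the Poisson test has its nominal size; the correlation between the two test statistics, which the protocol does not give, is varied.

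**1. Reproducing the plan's own figures.** Given the total number of cases n, the vaccinee count X is binomial. With no efficacy p = 0.5; with 70% efficacy p = 0.3/1.3 = 0.2308.

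- At n = 28, P(X ≤ 8 | 0.5) = 0.0178 and P(X ≤ 9 | 0.5) = 0.0436. The test therefore rejects at 8 or fewer vaccinee cases, which matches the last row of the protocol's table (20 to 8). A 19-to-9 split gives a lower limit of −9.9%.
- Power at 28 cases is P(X ≤ 8 | 0.2308) = 82.2%, consistent with the stated 80%.
- At n = 43 the test rejects at 14 or fewer, with power 94.7% for a lower limit above 0. The chance of a lower limit above 20% is 82.6%, again consistent with the stated 80%.

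**2. Actual size of the Outcome 1 test.** The exact test is conservative. Its two-sided size is 2 × 0.01785 = 0.0357 at 28 cases and 2 × 0.01577 = 0.0315 at 43.

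**3. Chance of at least one false significant result, independent tests.** The formula is 1 − (1 − a₁)(1 − a₂).

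- Two-sided, 28 cases: 1 − 0.9643 × 0.95 = 8.4%.
- Two-sided, 43 cases: 1 − 0.9685 × 0.95 = 8.0%.
- Benefit direction, 28 cases: 1 − 0.98215 × 0.975 = 4.2%.
- Benefit direction, 43 cases: 1 − 0.98423 × 0.975 = 4.0%.

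The comparator for one test in the benefit direction is a nominal 2.5%. Ignoring the conservatism of the exact test gives 1 − 0.95² = 9.75% two-sided, which is a nominal ceiling only.

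**4. Correlated tests.** Some invasive cases will also be pneumonia cases. The rate is 1 − P(|Z₁| < z₁, |Z₂| < z₂) under a bivariate normal, with z₁ set from the exact size and z₂ = 1.96.

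| Assumed correlation | 28 cases, two-sided | 43 cases, two-sided | 28 cases, benefit | 43 cases, benefit |
|---|---|---|---|---|
| 0 | 8.4% | 8.0% | 4.2% | 4.0% |
| 0.5 | 7.8% | 7.5% | 3.9% | 3.7% |
| 0.9 | 6.1% | 5.9% | 3.1% | 3.0% |

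To judge which row is plausible, approximate the correlation as shared cases / √(n₁ × n₂). If all 28 invasive cases were also pneumonia cases and there were 112 pneumonia cases (an assumed four-fold ratio), it would be 28/√(28 × 112) = 0.5. With 200 pneumonia cases it would be at most 28/√(28 × 200) = 0.37. The first two rows are therefore the relevant ones if pneumonia is at least four times as common as invasive disease.

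**The case against.** The strongest reply is that the protocol already ranks its outcomes. Section IX.A rests the efficacy estimate on invasive disease, section IX.B ties the hypothesis of no efficacy to that outcome alone, and the trial is sized on it. If Outcome 1 alone carries the efficacy claim, the error for that claim is 3.6% two-sided at 28 cases and nothing is inflated. This stands as a fair reading of intent. It does not settle the matter, because a role is not a condition on a test: Outcome 2 keeps the primary label and its own 0.05, and the wording elsewhere does not follow the ranking.

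A second reply is that multiplicity is often left to the statistical analysis plan, which is not shown and may deal with it. That limits the point but does not remove it, since the protocol itself fixes the level of each primary test.

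A third is that the two objectives ask separate questions, each entitled to its own 5%. That position can be defended, but the protocol would have to take it.

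Two stronger readings are tempting. A reader might infer that the protocol promises an overall 5% and breaks it; no overall level is stated anywhere. A reader might also infer that a significant pneumonia result alone would be declared a primary success. No section says so. The word joining the two case types in the efficacy definitions may simply list what is counted.

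The inflation also needs both nulls to be true. If the vaccine does prevent invasive disease, only the pneumonia null can be falsely rejected, at 5%.

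**Conclusion.** The point holds as an ambiguity in the testing scheme, with a modest effect on error. If either outcome may support a primary claim and the vaccine affects neither, the chance of at least one false significant primary result is about 8% two-sided: 7.8 to 8.4% at 28 cases and 7.5 to 8.0% at 43, for correlations from 0.5 down to 0. For a false claim of benefit it is about 4%, against a nominal 2.5% for one test. The result rests on the assumed correlation and on the Poisson test holding its nominal size. It contradicts no figure in the protocol. It is worth correcting because the remedy is cheap and the ranking it needs is already implied by section IX.A.

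**What to change.** In sections IX.A and IX.B, state the existing emphasis as a fixed sequence:

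1. Test Outcome 1 first; it succeeds if the exact two-sided 95% lower limit for efficacy is above 0.
2. Test Outcome 2 at two-sided 0.05 as a confirmatory claim only if Outcome 1 is significant.
3. Otherwise report the Outcome 2 estimate and its 95% confidence interval as supportive.

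Align the efficacy definitions in the Protocol Summary and section V.F.3 with this order.

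The sequence holds the chance of any false primary claim at or below 5%. It needs no extra children or analyses and leaves Outcome 1's power and the 28- and 43-case targets unchanged. By comparison, splitting alpha equally (0.025 each) would lower the rejection limit at 28 cases from 8 to 7 vaccinee cases and cut power from 82.2% to 69.0%.

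The cost falls on pneumonia, which cannot be claimed as confirmatory when Outcome 1 misses. Under the plan's own 70% efficacy that is 100 − 82.2 = about 18% of trials if analysed at 28 cases, and 100 − 94.7 = about 5% at the planned 43.
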